#### Sessions Two and Three

Couples in the intervention arm will attend two additional visits consisting solely of adherence counseling at 8 and 10 weeks after their first CHTC visit. Based on the efficacious Partner STEPS intervention, CHTC counselors utilize motivational interviewing to improve ART adherence among HIV-positive individuals. The Partner STEPS intervention was developed by drawing from relationship-oriented theory, existing efficacious individual-level ART adherence interventions, couple-focused HIV prevention interventions, and expert consultation. New content was incorporated to address all aspects of the HIV care continuum (eg, linkage to, and retention in, care) and to draw on relationship strengths through interactive activities. The theory-based Partner STEPS intervention is delivered by a trained bachelors-level counselor (interventionist). Each session is designed to use relationship strengths to increase motivation for HIV care and treatment, and cover sequential intervention *steps* relating to specific challenges in HIV care engagement and barriers to ART adherence. For each step, couples work with a trained interventionist to identify their unique challenges, actively problem-solve with the interventionist, and articulate and commit to working together to implement a plan in which each partner agrees to complete specific tasks. Partner STEPS counseling focuses on dyadic strategies to improve medication adherence and retention in care at each of ten *steps* for which Partner STEPS is named. Each step is a portion of HIV care that can present a challenge to those seeking care. The ten steps are: (1) transportation to appointments; (2) obtaining medications; (3) communicating with providers; (4) storing and transporting medications; (5) having a daily medication schedule; (6) coping with side effects; (7) adherence, self-care, and your relationship; (8) communicating within your relationship; (9) managing your social life and other relationships; and (10) dealing with privacy and disclosure. The counselors are trained to keep the focus on the couple by engaging both partners in problem solving and plan development. For sero-discordant couples, counselors are trained to focus the discussion on how *the couple* can *work together* to keep the HIV-positive partner healthy and to prevent transmission to the HIV-negative partner through medication adherence. Strategies to improve medication adherence and retention in care are tailored to the couple’s unique relationship, as the counselor asks the couple to consider strategies that may work best based on their relationship needs, context, and unique health situation. Bazzi et al describe the protocol for developing and testing of the Partner STEPS intervention [16].

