### Biomedical Measures

For HIV-negative partners, HIV sero-status is tested at each study assessment. For HIV-positive partners, viral load and ART levels are measured at each study assessment and collected via dried blood spots. All participants are tested for syphilis at each study assessment in the Atlanta and Chicago sites. Budgetary constraints prevented testing for other STIs, as well as syphilis testing, in the Boston site.

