### Outcomes

The primary outcomes are the HIV-positive partner’s engagement in HIV care and his achievement of viral suppression. Engagement in care is conceptualized as also including linkage to care and retention in HIV care. For HIV-positive partners who report no engagement in HIV care at baseline, linkage to care is defined as attending at least one clinical care appointment, having at least one CD4 test performed, and having at least one viral load test performed within 3 months of the baseline visit. Retention in care is measured by determining participation in continuous care; that is, at least two or more routine HIV visits at least three months apart, receiving two or more CD4 tests, and receiving two or more viral load tests within a 12-month period [58]. At each study visit, a blood draw will be conducted to provide a measure of the HIV-positive partner’s viral load and to test levels of ART. To supplement the viral load and ART-level biological markers, self-reported ART adherence is collected in each of the surveys. The AIDS Clinical Trial Group (ACTG) questionnaire includes items measuring adherence to medications for the past 4 days, adherence to scheduled instructions during the last weekend, and when any medication was last skipped. The questionnaire responses are weighted to calculate an adherence level from 0-100. The surveys also measure barriers to adherence via a 24-item scale based on the ACTG assessment for barriers to adherence to ART [59]. Participants are asked to note (using a scale ranging from *never* to *often*) if they missed their HIV medication over the past month for one of the provided reasons.

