### Statistical Analyses

The analysis employs an intent-to-treat analysis design. The percentage of HIV-positive individuals who achieve viral suppression and report being fully engaged in care will be compared across arms, using Chi-square tests for significant difference. Retention in care is measured as the number of 6-month blocks during which at least one clinic visit was attended over the 2-year period following an initial attended visit; the percentage of HIV-positive individuals who report full retention in care (one clinic visit during each 6-month block) and the number of 6-month blocks during which care was received will be compared across study arms, using the appropriate tests for statistical significance. The capability of the intervention to yield longer-lasting effects in adherence endpoints over time will be examined. The visual analog scale data over the course of the study, at baseline and follow-up, will be analyzed using generalized linear models (GLMs) with properly-chosen (based on the distribution of dependent variables) link functions to analyze longitudinal adherence outcome data. The GLMs will be estimated using generalized estimating equations (GEE) with robust standard error estimates, which provide an extension of regression analyses to the cases of correlated or repeated observations and allows for inclusion of both categorical and count-dependent variables, and for appropriate modeling of covariance structures when observations are correlated across time. With appropriate link functions, GLMs can readily handle dependent variables with normal distributions, dichotomous outcomes, count data (Poisson distribution), and over-dispersed or zero-inflated count data (negative binomial models). The models will include the dyadic characteristics scales to examine the extent to which adherence is shaped by relationship functioning.

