### Sample Size

Estimating 80% retention, we propose to enroll a sample of 165 male sero-discordant couples. The primary outcomes are engagement in HIV care and viral suppression. A sample of 165 sero-discordant couples provides statistical power (with 95% confidence and 80% power) to detect scientifically significant relative differences of 15%, 20%, and 25% in each of these outcomes between the two study arms. Additional health-enhancing behaviors include recent sexual risk-taking; using the data from our previous RCT of CHTC, this sample of 165 sero-discordant couples provides statistical power to identify significant differences in sexual risk-taking between the two arms. Using the methods described by Rosner for sample size estimation for longitudinal studies [67], a sample size of 75 couples in each group will ensure statistical power (using a two-sided two-sample t-test) to identify differences in the dyadic scale constructs between arms. As secondary outcomes, the study will examine sero-conversion and syphilis incidence between the two arms, although the power is insufficient to detect significance differences between the study arms.

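### Adherence, engagement and retention are analyzed from self-report in an unblinded trial that counsels one arm on those behaviors, and the ART drug level measured at every visit is not named in any stated arm comparison

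*Protocol article*

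**What the plan says.** All places are in the protocol article.

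- **Primary outcomes (Sample Size):** "The primary outcomes are engagement in HIV care and viral suppression".
- **Primary comparison (Statistical Analyses):** HIV-positive men who "achieve viral suppression and report being fully engaged in care will be compared across arms, using Chi-square tests for significant difference".
- **Retention (Statistical Analyses):** the compared quantities are "the percentage of HIV-positive individuals who report full retention in care (one clinic visit during each 6-month block") and the number of 6-month blocks with care. No clinic, chart or laboratory source is named.
- **Adherence over time (Statistical Analyses):** the data named for the GEE-estimated models are those of a visual analog scale.
- **Role of self-report (Outcomes):** "To supplement the viral load and ART-level biological markers, self-reported ART adherence is collected in each of the surveys".
- **Measured markers (Biomedical Measures):** for HIV-positive partners, "viral load and ART levels are measured at each study assessment and collected via dried blood spots".
- **What one arm is counseled on (Sessions Two and Three):** "Partner STEPS counseling focuses on dyadic strategies to improve medication adherence and retention in care". The Intervention section adds boosters at 6, 12 and 18 months, and Follow-Up Visits places a survey at those same visits.
- **What the other arm gets (Control Group; Follow-Up Visits):** information on ART and adherence, but no adherence counseling.

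**The concern.** Couples cannot be blinded to whether they are counseled jointly or separately. Intervention men work out plans for care attendance and medication with a counselor and their partner, commit to them, and later answer study questions on the same behaviors. That creates a pressure on reporting that arises after assignment and differs by arm, so randomization does not balance it. It bears on one of the two primary outcomes and on the adherence endpoint.

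The Control Group section concedes that unequal contact may produce an attention effect. It does not mention differential reporting.

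The article also ranks its evidence in two ways. Outcomes puts the biological markers first and self-report behind them. Statistical Analyses specifies a model for self-reported adherence and does not mention the drug level that self-report was meant to supplement.

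**Working it through.** **1. The sections side by side.** ART level is collected at every assessment (Biomedical Measures) and outranks self-report (Outcomes). From Statistical Analyses through the safety paragraph, the stated arm comparisons cover viral suppression, reported engagement, reported retention, visual analog scale adherence, dyadic scales, at-risk sex, sexual agreements, HIV and syphilis, partner violence and dissolution. ART level is not among them. The article does not describe the visual analog scale; I take it to be self-rated, as such scales are.

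**2. The plan's own figure.** Sample Size claims 80% power at 95% confidence for relative differences of 15%, 20% and 25%, with 165 couples and 80% retention. No control rate is given, so this cannot be reproduced. Assuming 1:1 allocation, 165 × 0.80 / 2 = 66 men per arm. Solving a two-sided 5% two-proportion test for the control rate that gives 80% power yields about 86%, 80% and 73% for the three differences. These rates serve only to show which base rates are compatible with the claim.

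**3. Size of a spurious difference.** Let true retention be *p* in both arms. Let a fraction *f* of non-retained intervention men report full retention, with accurate reporting in control. Then:

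- spurious difference = (1 − *p*) × *f*
- spurious relative difference = (1 − *p*) × *f* / *p*

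The 51% is the share remaining in care quoted in the Introduction. The other values of *p*, and all values of *f*, are assumptions.

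| *p* | *f* = 15% | *f* = 25% |
|---|---|---|
| 86% | 0.14 × 0.15 = 2.1 points; 2.4% relative | 3.5 points; 4.1% |
| 80% | 0.20 × 0.15 = 3.0 points; 3.8% | 5.0 points; 6.3% |
| 60% | 0.40 × 0.15 = 6.0 points; 10.0% | 10.0 points; 16.7% |
| 51% | 0.49 × 0.15 = 7.4 points; 14.4% | 12.3 points; 24.0% |

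**4. Effect on the test.** With *n* = 66 per arm and no true effect, set *p*₁ = *p*, *p*₂ = *p* + (1 − *p*)*f* and *d* = *p*₂ − *p*₁. The rejection probability is Φ((*d* − 1.96 *s*₀)/*s*₁) + Φ((−*d* − 1.96 *s*₀)/*s*₁), where *s*₀ is the pooled and *s*₁ the unpooled standard error.

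- For *p* = 51% and *f* = 20%: *p*₂ = 0.608, *d* = 0.098, *s*₀ = 0.0864, *s*₁ = 0.0860. This gives Φ(−0.83) + Φ(−3.11) ≈ 0.20, against a nominal 0.05.
- At the same *f*, the rate is about 16% at *p* = 60%, 12% at 70% and 9% at 80%.

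**The case against.** **The ART-level comparison may sit elsewhere.** The article is condensed and no SAP is shown. Statistical Analyses speaks of adherence endpoints in the plural and allows for dichotomous outcomes. This stands in part: a reader might infer that ART level will never be compared by arm, and the article does not establish that. What remains is that the one adherence measure it does name is the one Outcomes treats as the supplement.

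**An objective primary outcome already exists.** Viral suppression comes from blood and is compared by arm. The primary sentence can even be read as a joint endpoint of suppression and reported engagement, in which over-reporting could not turn an unsuppressed man into a success. This stands. It confines the weakness to engagement, retention and adherence. A reader might fear that better reported engagement with flat suppression would be declared a success, but no section says so.

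**Controls feel some pressure too.** They receive adherence information, and couples in the cohort get bi-monthly calls that assess adherence. This stands as a matter of degree: the counseling and commitments remain in one arm only.

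**The size rests on chosen inputs.** This stands. A reader might conclude that the bias matches the 15% difference in Sample Size. That holds only at low assumed retention. At the 86% control rate needed for 80% power at that difference, it is 2-4%.

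**Study viral load tests.** A reader might think the study's own tests satisfy the retention definition in Outcomes ("receiving two or more CD4 tests, and receiving two or more viral load tests within a 12-month period"). That definition also needs routine visits and CD4 tests, the retention measure in Statistical Analyses counts visits only, and any effect would fall on both arms. It does not support a claim of differential bias.

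**Conclusion.** The point holds for the self-reported outcomes. The stated adherence analysis is at odds with the article's own ranking of evidence, and reported engagement and retention are open to over-reporting that would tend to favor the counseled arm.

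The size is unknown, because the article gives no misreporting rate and no control rate. Under the assumed 15-25% over-reporting, it runs from about 2-4% relative where true retention is high (86%) to 14-24% at the 51% background rate. It also assumes accurate reporting in control; over-reporting there as well would shrink the gap.

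The documents do not support extending this to viral suppression or to the primary analysis as a whole, nor do they require that engagement lose its primary status.

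**What to change.** In Statistical Analyses:

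- Name dried-blood-spot ART level, compared between arms at each visit with the GEE model already planned, as the main adherence outcome.
- Keep self-reported adherence as supportive, which brings the section into line with Outcomes.
- Keep engagement in care as a primary outcome, but label it as self-reported and state that it will be interpreted alongside measured viral suppression and ART level.

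The cost is small: samples and assays are already planned, so this is a change to the analysis text. There are two drawbacks. ART level reflects recent dosing only, so it is not a full record of adherence between visits. It also needs an analysis cut-off, which the article does not give and which should be fixed before outcome data are compared by arm.

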The intervention is grounded in Couple’s Interdependence Theory [57], a framework that combines both interdependence theory and communal coping perspectives. The framework guides the selection of measures of behaviors and behavior change within the couple. These measures relate to our intervention in two ways. First, some aspects of communication and decision-making within the partnership may influence the efficacy of the intervention; couples with more constructive communication styles may benefit more from CHTC and achieve greater linkage to, and retention in, HIV care than couples with less constructive communication styles. Second, some aspects of partnerships, such as efficacy around implementing behavioral change, may actually be modified by the intervention. In these cases, changes in key characteristics of the partnerships may be in the causal pathway between the intervention and the adoption of ART, linkage to care, and safer behaviors within the partnership. We thus conceptualize the causal pathways as follows. Couples exposed to the intervention package will receive opportunities to talk about HIV, safer sex, and care-seeking within their relationship jointly with a qualified CHTC counselor. Relative to couples exposed to individually-focused testing and adherence counseling, exposure to CHTC may in turn impact communal coping, use of coping, and transformation of motivation, leading to initiation and maintenance of health-enhancing behavior (which we conceptualize as greater uptake and retention in care and ART adherence), lowering of sexual risk-taking inside and outside of the relationship, and a resultant lowering of sexually transmitted infection (STI) and HIV incidence. In our research design, predisposing factors, outcome efficacy, and couple efficacy will be collected separately from both partners before the HIV testing intervention is delivered, and will again be collected at each of the follow-up visits.

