#### Dyadic Characteristics

The four elements of Lewis’ model [57] (*predisposing factors of couples*, *partner’s transformation of motivation*, *process of communal coping*, and *use of communal coping*) are referred to as *dyadic characteristics*. In a recent RCT of CHTC, scales were developed to capture these constructs; all scales showed strong reliability, and evidence for construct validity was obtained for all scales [60]. In this intervention, each of the scales is collected in the baseline and follow-up surveys.

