The analysis will also examine conceptual mediators and epidemiologically identified moderators. If the Stronger Together intervention works to increase viral suppression and number of participants reporting full engagement in care among the intervention sample in significantly greater magnitude than the comparison condition, we will assess the extent to which this relationship works through several possible mediators, including dyadic factors and relationship functioning (ie, communication). For mediation analyses, we will employ MEDIATE procedures. MEDIATE estimates the total, direct, and indirect effects of causal variable(s) on the outcome variable through a proposed mediator variable or set of mediator variables. For effect modification (moderation) analyses, we will add interaction terms one-by-one for the intervention condition and the potential moderators (eg, age, race/ethnicity, and psychosocial factors such as depression and length of relationship). Significant or large interaction terms would suggest that the effects of the intervention differ for different subgroups, as defined by the moderators.

The analysis will also examine HIV sero-conversion among HIV-negative partners and syphilis as secondary outcomes: the prevalence and 24-month cumulative incidence of HIV and syphilis will be examined in aggregate and then by study arm. During the interim assessment visits (that occur before month 12 and then again before month 24) we will collect information on STI testing/diagnosis/treatment that participants received elsewhere since their last study assessment visit. These data will be used to adjust analyses. Using Cox proportional hazard regression models, we will assess if intervention status results in decreased odds (hazard ratio) of HIV and STI infection, separately, over the 24-month period.

The safety of the intervention at the individual level will be assessed by examining reported IPV within the relationship and relationship dissolution. Prevalence of each individual adverse outcome or any adverse outcome will be calculated, and prevalence of outcomes will be compared in the control and intervention groups using Chi-square tests or Fischer’s exact tests, as appropriate.

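### The only longitudinal adherence model described includes the dyadic scales without limiting them to baseline, so its arm coefficient may not be the intent-to-treat effect on adherence

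*Protocol article*

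**What the plan says.** **The adherence model.** The Statistical Analyses section declares an intent-to-treat analysis and introduces the longitudinal adherence analysis with its aim: "The capability of the intervention to yield longer-lasting effects in adherence endpoints over time will be examined". On the data, it says: "The visual analog scale data over the course of the study, at baseline and follow-up, will be analyzed", using generalized linear models fitted by GEE. On covariates, it says: "The models will include the dyadic characteristics scales to examine the extent to which adherence is shaped by relationship functioning". It describes no adherence model without the scales and does not say whether baseline or follow-up values enter.

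**The scales.** The Dyadic Characteristics section uses that name for four elements: predisposing factors, transformation of motivation, and the process and the use of communal coping. It adds that "each of the scales is collected in the baseline and follow-up surveys". The Introduction gives partnership characteristics two roles. Some may modify how well the intervention works. For others, "changes in key characteristics of the partnerships may be in the causal pathway between the intervention and the adoption of ART". The Introduction then names communal coping, its use and transformation of motivation as things CHTC may affect, leading to behavior that includes ART adherence.

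**Other uses of the scales.** The section on analysis of the scale data over time treats them as outcomes, compared by arm at each visit. The mediation paragraph, which follows the at-risk sex analysis, lists dyadic factors as candidate mediators: "we will assess the extent to which this relationship works through several possible mediators".

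**The adherence measures.** The Outcomes section describes the ACTG questionnaire ("The questionnaire responses are weighted to calculate an adherence level from 0-100"), a barriers scale and ART levels. It mentions no visual analog scale.

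**The concern.** In a randomized comparison, the total effect of assignment is estimated without conditioning on anything the assignment can change. The scales in this model include constructs that the article says the intervention may change on the way to adherence. If their follow-up values are covariates, the arm coefficient answers a different question: what effect remains with relationship functioning held fixed. That quantity is smaller than the total effect whenever the intervention works through the relationship, which is its stated theory. It is also no longer protected by randomization, because unmeasured factors that influence both relationship functioning and adherence can bias it.

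Improved adherence is part of the article's stated objective, and this is the only longitudinal test of it described. A null or reduced arm coefficient could be read as no lasting effect on adherence when the effect simply runs through the scales.

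A second, smaller matter is that the outcome named for this model is not among the adherence measures that the Outcomes section describes.

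**Working it through.** **1. Is the model restricted to pre-randomization values?** The text sets no restriction. Both baseline and follow-up values exist. The at-risk sex analysis says explicitly that its covariates are baseline ones, whereas the adherence paragraph does not. The outcome series runs over baseline and follow-up, so entering the scales visit by visit is a natural reading, though not the only one.

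**2. Are the constructs on the possible pathway?** Three of the four elements (transformation of motivation, process and use of communal coping) match what the Introduction says CHTC may affect before adherence. The fourth, predisposing factors, is partly treated as a modifier. So some of the scales are possible mediators, but not all.

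**3. Does another analysis supply the total effect on adherence?** The mediation analysis concerns viral suppression and engagement in care, and is conditional on an effect there. The primary chi-square tests concern the same two outcomes. Neither estimates the effect on adherence.

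**4. Size: arithmetic on assumed inputs.** The article gives no power for the adherence model, so there is no figure to reproduce. Assume that a two-sided 5% test of the total effect has 80% power. Its non-centrality is then 1.96 + 0.84 = 2.80. Let *m* be the mediated share, with the standard error held fixed. Power for the arm coefficient given the follow-up scales is Φ(2.80 × (1 − *m*) − 1.96):

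| *m* | calculation | power |
|---|---|---|
| 0 | Φ(2.80 − 1.96) = Φ(0.84) | 0.80 |
| 0.25 | Φ(2.10 − 1.96) = Φ(0.14) | 0.56 |
| 0.50 | Φ(1.40 − 1.96) = Φ(−0.56) | 0.29 |
| 0.60 | Φ(1.12 − 1.96) = Φ(−0.84) | 0.20 |

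**5. Size: simulation.** From the Sample Size section: 165 couples × 0.80 retention = 132 HIV-positive partners, or 66 per arm. Four follow-up visits, exchangeable GEE with robust standard errors, 300 replicates. Assumed: true total effect 0.5, arm effect on the scale 0.5 SD, and no confounding between scale and adherence. Entries are the mean arm coefficient, with the share of replicates at p < 0.05 in brackets:

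| mediated share | no scale | baseline scale | follow-up scale |
|---|---|---|---|
| 0% | 0.51 (0.97) | 0.51 (0.95) | 0.51 (0.97) |
| 25% | 0.51 (0.95) | 0.48 (0.95) | 0.38 (0.79) |
| 50% | 0.51 (0.94) | 0.49 (0.94) | 0.25 (0.44) |
| 75% | 0.50 (0.88) | 0.50 (0.93) | 0.14 (0.19) |
| 100% | 0.50 (0.80) | 0.50 (0.87) | 0.00 (0.05) |

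With follow-up scales, the coefficient tracks 0.5 × (1 − mediated share). With baseline scales it stays at the total effect apart from simulation noise. Rejection rates differ from step 4 because the simulated test starts from higher power. Confounding between mediator and adherence would add bias that neither calculation includes.

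**6. The outcome.** The visual analog scale appears only in the Statistical Analyses section. The Outcomes section gives the ACTG 0-100 score, built by weighting questionnaire items, and ART levels. The two sections do not name the same adherence outcome.

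**The case against.** The strongest reply is that the article never says follow-up values enter. Baseline values are available, using them costs nothing, and the coding of covariates is often left to an analysis plan, which is not shown here. The reason given for including the scales is explanatory: learning how relationship functioning shapes adherence requires having it in a model. The text speaks of models in the plural and does not forbid one without the scales. The primary outcomes are tested without them, and self-reported adherence only supplements the biological markers. The Introduction says *may*, and gives some characteristics a modifying role.

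Most of this stands, and it limits the point. A reader might infer that the model adjusts the intervention effect away. The documents do not support that: the loss needs follow-up values in the model and covers only the mediated share. Nor do they place all the dyadic scales on the pathway.

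A reader might also infer that no visual analog scale is collected, or that the ACTG score and ART levels go unanalyzed. Neither can be shown. The survey is not itemized, and the reference to adherence endpoints in the plural could cover both measures.

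What the reply does not remove is that the text puts the scales into the one adherence analysis it describes, under an intervention-effect aim and without restriction. An explanatory question and a total-effect question need two models.

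**Conclusion.** The point holds as a fault of specification in a non-primary analysis. As written, the adherence analysis permits a model whose arm coefficient is a direct-type effect, open to confounding, under a heading that declares intent to treat. The comparisons of viral suppression and engagement in care are untouched.

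The size cannot be taken from the documents. On the assumption of 80% power for a total-effect test, power is about 29% with half the effect mediated. It is unchanged at 80% with nothing mediated, and entering the scales at baseline only causes no attenuation. The mediated share, the starting power and the simulated effect sizes are all assumptions. The mismatch between the visual analog scale and the described adherence measures is an inconsistency between two sections and supports a request to reconcile them, nothing more.

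**What to change.** 1. State that the intervention effect on adherence is estimated by a GEE model containing arm, visit and arm-by-visit, with dyadic scales entered at baseline values only, if at all.
2. Put the follow-up scales in a separate model labelled as explanatory or mediation. State that its arm coefficient is not the intent-to-treat effect and that its interpretation requires no unmeasured confounding between the scales and adherence.
3. Reconcile the Statistical Analyses and Outcomes sections so that the analyzed adherence outcome is one the measures section describes: either add the visual analog scale there, if it is collected, or name the ACTG score or ART level as the model outcome.

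The cost is a few sentences. No new data are needed for the first two changes, because both baseline and follow-up scales are already collected. The third needs only a check of which instruments the survey contains.
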